### Participants: selection of cases & controls

#### **
*CC1 & CC2*
**

*Population of dead cases (A)* All women who died of primary breast cancer (as stated in part 1 of the death certificate) age 47–89, within the specified 2-year study period will be selected. Cases of women with only in situ primary breast cancer records (i.e. no invasive record) will be included, but Death Certificate Only (DCO) cases will be excluded. Case A women will have had their date of first diagnosis of primary breast cancer (in situ or invasive) age 47–89 and since 1990, and for subsequent phases of this evaluation (main phase onwards), they will not have been included as cases in previous evaluation periods, although they may have been included as controls, and may also be selected as a case C in the same evaluation.

*Population of cases A-matched general population controls (B)* For each case A, two women will be selected among the general population in the Health & Social Care Information Centre (HSCIC) database at Exeter who, are registered in the same National Health Applications and Infrastructure Services (NHAIS) system as the case at the case’s date of first diagnosis, are alive at the case’s date of death, and were born within 1 month either side of the case’s date of birth. Control B women may have had primary breast cancer (in situ or invasive) at the case’s date of first diagnosis. For subsequent phases of this evaluation (main phase onwards), they will not have been included as population controls B, E, or D in previous evaluation periods, although they may be included as a controls E or D within the same evaluation period.

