*Population of cases A-matched diseased controls (E)* For each case A, one woman will be selected among the CR population who was alive at the case’s date of death, and was born within 1 month either side of the case’s date of birth. DCO cases will be excluded. Control E women will have had primary invasive breast cancer diagnosed within 2 months prior to *and including* the case’s date of first diagnosis and: this is necessary to ensure that the control survived for at least as long as the cases. She will have been registered in the same Cancer Network (CN) at the case’s date of first diagnosis. If no control E is found using this criterion, the date range will be expanded to 3 months prior to the case’s date of first diagnosis (or 6 months prior, if the case’s age at first diagnosis is less than 50 or over 70). For subsequent phases of this evaluation (main phase onwards), they may have been included as population controls B or D in previous or within the same evaluation periods, and may be included as a case C within the same evaluation period.

#### **
*CC3a, CC3b & CC4*
**

*Population of incident cases (C)* All women who have had primary breast cancer (in situ or invasive), diagnosed age 47–89 within the specified 2-year study period will be selected. The **index diagnosis** will be either a first or a subsequent tumour and, therefore, women may have had a previous history of in situ or invasive primary breast cancer (i.e. prior to the date of their index diagnosis). Case C women may have died from primary breast cancer (as stated in part 1 of death certificate) age 47–89 during the specified 2-year study period, or afterwards. Cases of women with in situ primary breast cancer records only (i.e. no invasive record) will be included, but DCO cases will be excluded. For subsequent phases of this evaluation (main phase onwards), they will not have been included as cases in previous evaluation periods, although they may have been included as controls, and may also be selected as a case A in the same evaluation.

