*Population of cases C-matched general population controls (D)* For each case C, two women will be selected from the general population in the HSCIC database at Exeter who, are registered in the same NHAIS system as the case at the case’s date of index diagnosis, are alive at case’s date of index diagnosis, and were born within 1 month either side of the case’s date of birth. For subsequent phases of this evaluation (main phase onwards), they will not have been included as population controls B, E, or D in previous evaluation periods, although they may be included as controls B or E within the same evaluation period.

Incident cases (C) and matched general population controls (D) will be selected *a posteriori* by the PRU, using tumour information, to suit the purpose of each case-study (see Figure 1).

**For CC3a**, incident cases (C) will be restricted to those women with invasive breast cancer, and matched general population controls (D) will be restricted to those women who have never had invasive primary breast cancer, but may have had in situ primary breast cancer prior to *and including* the case’s date of index diagnosis.

**For CC3b**, all incident cases (C) will be selected. For in situ cases, matched general population controls (D) will be restricted to those women who never had primary breast cancer (in situ or invasive) prior to *and including* the case’s date of index diagnosis; for invasive cases, to those women who never had invasive primary breast cancer, but may have had in situ primary breast cancer.

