Women who accept the invitation to screening (attenders) may have an a priori better health status (and a lower underlying risk of dying from breast cancer) compared with women who do not (non-attenders), and therefore are less likely to die from the disease. We would anticipate that this will confer a bias *in favour of* screening. Although this bias in favour of screening is unavoidable at the design stage, it can be approximately corrected for in the statistical analysis. In women diagnosed with breast cancer aged 47–52 (and their controls) we will look at two factors: “(invited and) screened”, “invited but not screened” compared to “not invited”. The odds ratio in “invited but not screened” can be used to adjust for the self-selection bias using the method by Duffy et al. (2002) [6]. This method cannot be used in older women as they will all have been invited.

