The method developed by Duffy et al. (2002) [6] will also be used to correct the estimated odds ratio using data on participation in the NHSCSP (cervical) and/or NHSBCSP (bowel) screening programmes, rather than data on participation from the RCTs of mammographic screening. In the absence of self-selection, the relative risk of primary breast cancer (death/incidence) associated with breast screening for non-attenders at cervical or bowel screening would be expected to be equal to the relative risk in cervical or bowel screening attenders (after adjusting for breast cancer screening). In practice, the relative risk of primary breast cancer has been shown to be about 10% lower in non-attenders to RCTs (Duffy et al., 2002 [6]). The crucial element in correcting for self-selection bias is the risk ratio (termed “Dr”) for non-attenders versus attenders to cervical or bowel screening. This will be calculated for women who attended breast screening at least once and for women who did not attend a single screen, to control for attendance at breast screening. A range of denominator values for “Dr” will be assessed for sensitivity. One could compare primary breast cancer rates (i) in women who have had bowel/cervical screening - but not breast screening -with women who have had neither bowel/cervical nor breast screening; and (ii) in women who have had *both* bowel/cervical and breast screening with women who have only had breast screening. Data for women with age at diagnosis/ pseudo-diagnosis between 47 and 64 year-old who would have been invited to both the breast and cervical screening programmes will be used. Alternatively, data for women with age at diagnosis/pseudo-diagnosis between 60 and 69 year-old who would have been invited to both the breast and bowel screening programmes will be used. Also, in women under age 50, one could compare primary breast cancer rates in women who have, or have not had, cervical screening, hence by-passing the positive confounding between uptake of the various screening programmes.

Breast screening coverage of women aged 53–70 in England was 77% at 31st March 2012 (The HSCIC Breast Screening Programme – England report, 2011-2012 [17]).

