### Statistical methods

All case–control study analyses will be conducted using conditional logistic regression. Matching factors (i.e. age, area) are controlled for in the design. All statistical analyses will be performed using the statistical software STATA or R.

**CC1.** The *primary objective* of this case–control will be to assess the effect of various measures of attendance at breast screening *strictly prior to* the case’s date of first diagnosis/ the control’s date of pseudo-diagnosis on mortality from primary breast cancer. The primary measure of attendance to screening will be whether a woman ever attended at least one screen episode (indicator variable). Secondary measures will be:

• the total number of screens (counts);

• the time since last screen (continuous variable), and whether that time span fell within the past three years (≤ 3 years or > 3 years), as this corresponds to the NHSBSP protocol and approximates the estimated PCDP;

• the time since penultimate screen (continuous or categorical);

• the interval between last screen and penultimate screen (continuous or categorical);

• the maximum interval between 2 screens (continuous or categorical);

• the average interval between 2 screens (continuous or categorical);

• the patient’s age at first screen (continuous or categorical);

• the patient’s age at last screen.

*Ascertainment, self-selection* and *exposure opportunity* biases will be addressed using the methods described in the *Bias & Effect modification* section.

**
*Secondary objectives*
** will consider time since last screen stratified by age at diagnosis/pseudo-diagnosis, by first tumour detection mode, and by region (Main phase only).

The effect of attending a screen in a particular 3-year age band in the main phase (such as 47–49 inclusive), or 5-year age band in the pilot phase, on mortality from primary breast cancer in the subsequent 5-year age band (such as 50–54) will also be investigated, as performed for the cervical screening audit (Sasieni et al., 2009 [22]). The results of this analysis should be very similar to those obtained from the analysis of “time since last screen” after stratifying the analysis by age at diagnosis/pseudo-diagnosis.

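### The optional under-50 self-selection comparison does not by-pass breast screening as claimed, because women under 50 in this study are aged about 47–49, ages the protocol treats as partly screened

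*Protocol article*

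**What the plan says.** In the Protocol article, the section Bias & Effect modification (self-selection bias) commits to a correction factor, Dr: the risk ratio for non-attenders versus attenders at cervical or bowel screening. Dr is to be calculated separately in women who did and did not attend breast screening. Two comparisons, (i) and (ii), are then sketched, and both hold breast screening fixed. The article adds that "in women under age 50, one could compare primary breast cancer rates in women who have, or have not had, cervical screening". It presents this as a shortcut that needs no control for breast attendance, "hence by-passing the positive confounding between uptake of the various screening programmes". No restriction to women who were uninvited or unscreened for breast cancer is attached to this last comparison.

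The ages come from Participants: selection of cases & controls. Dead cases have their "first diagnosis of primary breast cancer (in situ or invasive) age 47–89 and since 1990". Incident cases are those "diagnosed age 47–89 within the specified 2-year study period will be selected". General population controls "were born within 1 month either side of the case’s date of birth", with a wider window only when no match is found.

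**The concern.** The attraction of the under-50 comparison is that it would need no control for breast screening, because breast screening would not yet have begun. If some of these women have already been invited and screened, that advantage is lost. The article itself says that uptake of the programmes is positively related, so cervical attenders would be breast-screened more often than cervical non-attenders. Any effect of breast screening on incidence or mortality would then appear as a difference between the two cervical groups and be read as self-selection. An odds ratio corrected with such a factor would carry the error.

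**Working it through.** **Step 1: who is under 50.** Cases enter at 47 and controls share their birth date to within months. Women under 50 are therefore aged 47–49, apart from a few controls marginally under 47.

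**Step 2: how the article treats ages 47–49.**

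- Bias & Effect modification, shortly before the under-50 sentence: data for women aged "between 47 and 64 year-old who would have been invited to both the breast and cervical screening programmes will be used". This range contains 47–49.
- Statistical methods, CC1 secondary objectives: the plan will study the effect of "attending a screen in a particular 3-year age band in the main phase (such as 47–49 inclusive"), so these are ages at which screens are attended.
- Bias & Effect modification, first self-selection method: "In women diagnosed with breast cancer aged 47–52 (and their controls) we will look at two factors", namely screened and invited but not screened, each against not invited. All three groups are expected at these ages.
- Participants: the stated aim is to select women already invited at least once before diagnosis or pseudo-diagnosis. This is an aim, not a fixed rule.

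Together these show partial exposure to breast screening at 47–49. The by-pass would hold only if none of these women had been invited, or if breast uptake were equal in cervical attenders and non-attenders. The passages above contradict the first condition, and the article's own reference to positive confounding contradicts the second.

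**Step 3: size.** The article gives no figure for this comparison, so there is nothing to reproduce. Let f be the share of women under 50 already invited to breast screening, a1 and a0 the breast uptake of invited women among cervical attenders and non-attenders, and r the risk ratio in breast-screened women. With no self-selection, the true factor is 1 and the apparent factor is

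[1 + f·a0·(r − 1)] / [1 + f·a1·(r − 1)].

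Only r = 0.7 for mortality comes from the article (the CC1 odds ratio in Study size / Power calculation). Applying it at ages 47–49 is an assumption. All values of f, a1 and a0, and r for incidence, are also assumed.

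*Mortality, r = 0.7*

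| f | a1/a0 = 0.80/0.60 | a1/a0 = 0.85/0.50 |
|---|---|---|
| 0.10 | 1.006 | 1.011 |
| 0.25 | 1.016 | 1.028 |
| 0.50 | 1.034 | 1.060 |
| 1.00 | 1.079 | 1.141 |

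For example, at f = 1 with 0.80/0.60: (1 − 0.60 × 0.3)/(1 − 0.80 × 0.3) = 0.82/0.76 = 1.079.

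*Incidence, milder inputs, r = 1.3, f = 0.30*

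- 0.80/0.60: (1 + 0.054)/(1 + 0.072) = 0.983
- 0.85/0.50: (1 + 0.045)/(1 + 0.0765) = 0.971

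*Incidence, stronger inputs, a1/a0 = 0.80/0.40*

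| f | r = 1.5 | r = 2 | r = 3 |
|---|---|---|---|
| 0.10 | 0.98 | 0.96 | 0.93 |
| 0.30 | 0.95 | 0.90 | 0.84 |
| 0.50 | 0.92 | 0.86 | 0.78 |

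For example, at f = 0.30 and r = 2: (1 + 0.12)/(1 + 0.24) = 0.90.

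**Step 4: check of the remedy.** With f = 0 the expression equals 1 for every r, a1 and a0. The by-pass works once the comparison is confined to women not yet invited.

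**The case against.** The strongest reply is that the comparison is optional. It is introduced as something one could do, and no estimate is said to depend on it. The committed Dr is stratified by breast attendance, and comparisons (i) and (ii) also hold breast screening fixed. The plan further has the invited/not-invited method at 47–52, a sensitivity range for Dr and individual-level adjustment. All of this stands. A reader might infer that the corrected incidence and overdiagnosis results inherit the error; the article does not support that, since it would happen only if this option were chosen to supply the factor.

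A reader might also infer that the plan treats all women aged 47–49 as screened. It does not. It expects a not-invited group at 47–52, and the CC3a/b text (ages 65–69 after up to 15 years of screening) points to a start near 50. The 47–49 band is an example for the main phase. Exposure is partial and unquantified.

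Third, the larger figures rest on chosen inputs. The article expects an excess in incidence straight after a screen and then a deficit, so a three-fold ratio sustained across 47–49 is doubtful. That also stands.

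Finally, a condensed article may leave a restriction to the full protocol, and the rationale does presuppose women not yet exposed. But the article states the by-pass as a fact about women under 50, and its own age ranges contradict that. The justification as written is wrong, whatever detail exists elsewhere.

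**Conclusion.** The point holds for this one optional comparison. Among women aged 47–49, comparing cervical attenders with non-attenders without restriction or stratification does not by-pass the link between programme uptakes. If used, the factor would be biased even with no self-selection: below 1 for incidence if a first screen raises detection, above 1 for mortality if screening protects as the plan assumes. It would be wrong to infer a single direction for both outcomes.

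The size cannot be fixed from the article, because the invited share and uptake at 47–49 are not given. Under the assumptions above it runs from about 1–3% at low invited shares with milder inputs to more than 10% at high invited shares or with a strong first-screen effect. One incidence scenario (30% invited, two-fold ratio, uptake 80% against 40%) gives 0.90, the same size as the roughly 10% lower risk in non-attenders that the article cites from the trials. That is one chosen scenario, not evidence that the two effects match.

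**What to change.** Restrict the under-50 comparison to women with no breast screening episode opened before the diagnosis or pseudo-diagnosis date, using the Episode date field in Table 1 and the same rule for cases and controls. Selecting on an unopened episode does not select on a woman's decision to attend, so it adds no new self-selection. Alternatively, stratify the comparison by breast screening, as in (i) and (ii). If too few women remain, drop the comparison and the by-passing claim.

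The cost is one selection rule on data already to be collected, and fewer women in a secondary comparison. The loss could be large if the aim of selecting women already invited at least once is largely met. The committed Dr and comparisons (i) and (ii) need no change.

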### Setting & source population

The background, implementation and organisation of the NHSBSP are described in detail elsewhere (Advisory Committee on Breast Cancer Screening, 2006 [9]). For this study, all women who were invited to participate in the breast screening programme in England (from 1988 onwards), and who did not express dissent to their records being used for evaluation purposes, will be targeted.

The evaluation will begin with a pilot phase in collaboration with the Knowledge & Intelligence team London, KIT London (formerly Thames Cancer Registry), using cases that died from or were diagnosed with breast cancer between 1st of January 2008 and 31 of December 2009 in London. The main phase of the study will then be undertaken, which will cover the whole of England or, in the case of CC2, those regions (i.e. previous cancer registries) for which tumour attributes and treatment variables will be available from 1st of January 2010 - in collaboration with the Office for National Statistics (ONS). Each main phase evaluation will cover a 2-year period.

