Applying a restriction on the date of diagnosis during the selection of dead cases can also introduce a form of lead-time bias. Among cases who died from breast cancer on the same date, the screen-detected ones would have received their diagnosis earlier than the symptomatically-diagnosed cases, and therefore would tend to be excluded during the selection, introducing a bias in *favour of screening*. No restriction on the case’s date of diagnosis will be applied at the design stage, i.e. all women diagnosed after the inception of the NHSBSP, i.e. since 1990, will be included in the study.

#### **
*Length bias*
**

Length-biased sampling occurs when the chance of an observation being in a sample is proportional to a particular characteristic of the observation. In the context of screening, length bias is the phenomenon whereby slower-growing, less aggressive tumours (including DCIS) have a longer pre-clinical screen-detectable period (PCDP) and are therefore more likely to be screen-detected compared to faster-growing, more aggressive cancers. This will confer a bias *in favour of screening*, which will be addressed at the analysis stage of case-study 2 by performing sensitivity analyses. Two latent tumour populations will be assumed, one – the “length bias group” - with both a higher probability of being screen-detected and a correspondingly lower probability of fatality, whether actually detected by screening or symptomatic (Duffy et al., 2008b [19]).

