The extreme form of length bias is overdiagnosis, defined as the diagnosis of cancers which would not have come to clinical attention in the patient’s lifetime had screening not taken place. Overdiagnosis can be estimated by comparing cumulative incidence in screened and unscreened populations several years after screening stops (Biesheuvel et al., 2007 [21]). Estimates of overdiagnosis obtained from observational studies vary widely according to the design used, i.e. dynamic populations or cohort populations (Puliti et al., 2011 [16]). In case–control studies, which are nested within a cohort population, overdiagnosis can be robustly estimated provided that (1) the difference in underlying risk of primary breast cancer between screened and unscreened populations (i.e. self-selection bias), and (2) the period of time by which the diagnosis is brought forward by screening (i.e. lead-time bias) are both accounted for (Duffy et al., 2010 [13], Puliti et al, 2011 [16]). In the absence of overdiagnosis, the initial increase in primary breast cancer occurrence in the screened group would be fully compensated by a similar decrease in cancers among older age groups no longer offered screening (“compensatory drop method”, Puliti et al., 2011 [16]).

In addition to investigating the extent of the different biases when examining the relationship between screening and mortality or incidence, identifying homogeneous strata that may (positively or negatively) modify the effect of the screening exposure on the outcome (effect modifiers), such as age at diagnosis / pseudo-diagnosis (5-year band), epoch of diagnosis (5-year band), and tumour detection mode of the cases will be of interest.

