**CC2.** The *primary objective* of this case–control will be to estimate the proportional effects of screening attendance *strictly prior to* date of diagnosis/pseudo-diagnosis and cancer treatment, on prognosis in patients diagnosed with primary breast cancer. The primary and secondary measures of attendance to screening will be as for CC1; in addition, they will include tumour detection mode to assess the relationship between detection mode and choice of cancer treatment.

The regression analysis will be adjusted for tumour attributes such as stage of disease at diagnosis and other pathological features. Because of the extreme collinearity between cancer treatment and pathology variables, e.g. lymph node positivity, a major determinant of treatment choice, estimating relative effects from the regression analysis often gives unreliable/biased estimates of cancer treatment (Wishart et al., 2010 [23]). To address this statistical issue, a counterfactual analysis will be performed (Höfler et al., 2005 [24]). The treatment that an individual actually does not receive is called counterfactual treatment, and the outcome under this treatment, after treatment assignment, is referred to as counterfactual outcome. In our study, the cancer treatment effects will be constrained to the absolute effect estimated from meta-analyses of the RCTs.

*Self-selection*, *lead-time, and length* biases will be addressed using the methods described in the *Bias & Effect modification* section. Because in CC2, both cases and controls have had primary breast cancer, *exposure opportunity* bias can be assumed to be minimal.

**
*Secondary objectives*
** will consider time since last screen stratified by epoch of diagnosis to further explore collinearity among the explanatory variables.

**CC3a/b.** The *primary objectives* of these case-controls will be to estimate the effect attendance at breast screening strictly prior to date of diagnosis/pseudo-diagnosis on incidence of invasive (CC3a) or, of in situ and invasive (CC3b) primary breast cancer, and to estimate rates of overdiagnosis due to screening.

The primary and secondary measures of attendance to screening will be as for CC1, in particular time since last screen; in addition, they will include the patient’s age at last screen, and whether a woman ever missed attendance at recall assessment(s). This last measure should help assess potential room for improvement in the management of suspicious screening results.

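### Within one evaluation, 5-year epoch of diagnosis among the dead cases is a band of time from diagnosis to death, so a constant screening effect may appear to vary by epoch

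*Protocol article*

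**What the plan says.** Under Participants: selection of cases & controls, women who died of primary breast cancer "within the specified 2-year study period will be selected". Their diagnosis may lie far back: "Case A women will have had their date of first diagnosis of primary breast cancer (in situ or invasive) age 47–89 and since 1990". Setting & source population fixes the pilot as "using cases that died from or were diagnosed with breast cancer between 1st of January 2008 and 31 of December 2009 in London" and adds: "Each main phase evaluation will cover a 2-year period".

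The closing paragraph of Bias & Effect modification names possible effect modifiers, including "epoch of diagnosis (5-year band), and tumour detection mode of the cases will be of interest". Under Statistical methods, the CC2 secondary objectives "will consider time since last screen stratified by epoch of diagnosis to further explore collinearity among the explanatory variables". The CC1 secondary objectives list age at diagnosis, first tumour detection mode and region, but not epoch.

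The lead-time subsection warns: "Applying a restriction on the date of diagnosis during the selection of dead cases can also introduce a form of lead-time bias". Its reason, for cases that share a day of death, is this: "the screen-detected ones would have received their diagnosis earlier than the symptomatically-diagnosed cases, and therefore would tend to be excluded during the selection". It calls this a bias in favour of screening and therefore admits all diagnoses since 1990. The subsection on exposure opportunity bias says that lead-time and length bias affect only survival-type analyses, that is CC2. Accordingly, the biases to be addressed in CC1 are ascertainment, self-selection and exposure opportunity. CC2 has two planned lead-time corrections.

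**The concern.** Diagnosis date equals death date minus time from diagnosis to death. When every death falls within two years, choosing a diagnosis band amounts to choosing a survival band. An epoch stratum is therefore the kind of diagnosis-date restriction that the lead-time subsection set out to avoid. The recent band loses screen-detected cases, whose diagnosis was brought forward, and the older bands gain them.

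An epoch table could then suggest that screening has become more effective, or that it once did little or even harm, when nothing has changed. CC1 has no lead-time correction because the plan takes the bias to be absent there. In CC2 the diseased control must be alive when her case dies, so each epoch compares fatality at a different time since diagnosis, on top of any calendar change in treatment.

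**Working it through.** The plan gives no figure on this point to reproduce.

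**Step 1: survival range in each band.** Pilot deaths run from the start of 2008 to the end of 2009. The shortest possible time is 2008 minus the end of the band, but not below 0. The longest is 2010 minus its start.

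| Epoch | Shortest (years) | Longest (years) |
|---|---|---|
| 1990-94 | 2008 − 1995 = 13 | 2010 − 1990 = 20 |
| 1995-99 | 2008 − 2000 = 8 | 2010 − 1995 = 15 |
| 2000-04 | 2008 − 2005 = 3 | 2010 − 2000 = 10 |
| 2005-09 | 0 | 2010 − 2005 = 5 |

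Adjacent bands overlap by two years, so the identity holds to within the death window. In simulation the correlation of diagnosis date with diagnosis-to-death time is about −0.99.

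**Step 2: inputs for the CC1 odds ratio by epoch.**
- From the protocol: odds ratio 0.70 for ever attending (Study size / Power calculation), held constant here; deaths uniform over 2008-09; average sojourn time of 4 years for screen-detected cases (exposure opportunity bias), used as the upper value for mean lead time.
- Assumed, because the documents do not give them: exponential time from symptomatic diagnosis to death, median 3, 5 or 8 years; share q of attenders' fatal cancers that are screen-detected, 15-50%; exponential lead time with mean m of 1-4 years; attendance constant over time.

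**Step 3: formulas.** Let λ = ln 2 / median and μ = 1/m. The probability that diagnosis-to-death time exceeds t is
- non-attenders: S0(t) = exp(−λt)
- attenders: S1(t) = (1 − q)·exp(−λt) + q·[μ·exp(−λt) − λ·exp(−μt)]/(μ − λ)

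For a band from a to b, P(band) is the average over death dates u of S(max(u − b, 0)) − S(u − a). The expected odds ratio in the band is 0.70 × P1/P0.

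**Step 4: a middle case** (median 5 years, q = 30%, m = 4 years).

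| Epoch | P1 | P0 | 0.70 × P1/P0 |
|---|---|---|---|
| 1990-94 | 0.0908 | 0.0720 | 0.88 |
| 1995-99 | 0.1695 | 0.1440 | 0.82 |
| 2000-04 | 0.2966 | 0.2881 | 0.72 |
| 2005-09 | 0.3475 | 0.4238 | 0.57 |

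Unstratified: 0.70 × 0.9044/0.9279 = 0.68.

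**Step 5: range.** The pairs (q, m) were (30%, 1), (15%, 2), (30%, 2), (30%, 4) and (50%, 4), each with the three medians. The expected odds ratio is 0.49-0.66 in 2005-09, 0.72-1.55 in 1990-94 (1.55-1.56 by simulation) and 0.66-0.70 unstratified. At median 5 years, mild settings give, oldest to newest:
- q = 30%, m = 1: 0.73, 0.73, 0.73, 0.66
- q = 15%, m = 2: 0.74, 0.74, 0.72, 0.66
- q = 15%, m = 1, outside the five pairs: 0.72, 0.72, 0.72, 0.68

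**Step 6: is the cause isolated?** A separate simulation used 77% attendance, 40% or 60% of attenders' tumours screen-detected, and lognormal or exponential survival.
- With no lead time the odds ratios are flat.
- With a true value of 0.70 and lognormal survival, they run from 0.76, 0.78, 0.72, 0.65 (lead 2 years, 40%) to 1.15, 0.98, 0.74, 0.50 (lead 4 years, 60%).
- If deaths are instead counted within 10 years of diagnosis at any calendar date, the trend goes (0.69 in every epoch, or 0.61-0.62, for the same two settings).

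So the death window combined with lead time produces the trend. With the planned 1400 cases and 2800 controls, a 5% trend test would flag it with probability about 13% to 97% across these two settings.

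**The case against.** **Commitment.** The effect-modifier sentence names no study and offers epoch only as an example. The CC1 analysis section does not list it. A reader might infer that the plan commits CC1 to epoch strata; it does not. In CC1 the point concerns an exploratory item.

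**Purpose.** A reader might also infer that the plan promises a calendar-trend reading of the epoch strata. The stated aim in CC2 is to explore collinearity. The risk lies in how the strata would naturally be read.

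**CC2 protection.** Controls E are matched on diagnosis date, and lead-time correction is planned; one of its two methods shifts the diagnosis date of screen-detected cases. This may reduce the trend. It does not change the fact that each epoch compares fatality at a different time since diagnosis. The figures above are for CC1 and ever attending. They do not apply to CC2, whose analysis concerns time since last screen.

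**Size.** The 4-year sojourn time describes screen-detected cases in general. The length-bias subsection says slower-growing, less aggressive tumours stay detectable longer, so lead time in fatal cancers may well be shorter. The screen-detected share is not in the documents. The most extreme value, 1.55, arises in a band holding about 3% of non-attenders' deaths and would be very imprecise in the pilot. A claim that the trend will be steep is therefore not supported.

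What remains is the structural identity and the direction of the distortion, both of which follow from the protocol's own text.

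**Conclusion.** The point holds as a limit on interpretation. Within one evaluation, epoch of diagnosis cannot be separated from time from diagnosis to death beyond the two-year window. Lead time alone may then make a constant screening effect look more protective in recent epochs, and the plan gives CC1 no correction because it confines lead-time bias to CC2. Under the assumptions in Step 2 the size ranges from slight (for example 0.73 in the oldest band against 0.66 in the newest) to marked (1.55 against 0.50), with a constant true value of 0.70. No size is established for CC2.

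A reader might infer that the main mortality result is compromised. It is not: the unstratified odds ratio moves only from 0.70 to between 0.66 and 0.70. The incident-case studies are outside the point, because their index diagnoses all fall within the two-year period.

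**What to change.** State that, within a single evaluation, epoch of diagnosis will not be interpreted as a calendar effect modifier in CC1 or CC2. If the strata are shown, label them as time from diagnosis to death. In CC2, report them with the planned lead-time correction.

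Assess calendar change across the planned biennial evaluations. Compare the same band of time from diagnosis to death, for example 0-4 or 5-9 years, or the unstratified odds ratio, between successive death periods. The lead-time distortion is then about equal on both sides, provided that lead time and the screen-detected share have not changed much. The level within a band remains distorted, so only the comparison should be read.

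The cost is a change of analysis wording; the dates needed are already in Table 1. The drawback is that the pilot alone yields no calendar-epoch result, since at least two evaluations are needed.
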